#### Patient-reported outcomes

2.4.2

(Visual Analog Scale, Oswestry Disability Index, Japanese Orthopedic Association score, and 36-Item Short Form Health Survey) are inherently subjective and cannot be blinded, as participants are aware of their treatment assignment. Therefore, these outcomes are at risk of detection bias, which will be acknowledged as a limitation. Statistical analyses will be performed without knowledge of the actual group assignments, and unblinding will occur only after completion of all statistical analyses. Premature unblinding will not be permitted unless serious adverse events or other emergencies occur.

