#### Tuina group

2.6.1

The Tuina intervention comprised three standardized procedures targeting the lumbar–abdominal region. Firstly, all participants received standardized lumbar spine health education prior to the intervention. Subsequently, the Tuina procedures were performed with the participant in a supine position, with the hips and knees flexed.The procedures were carried out in the order of A–C (Figure 2), including rubbing, pushing, and acupressure techniques applied at predefined acupoints, namely Mingmen (DU4), Zhangmen (LR13), Daimai (GB26), Shenque (CV8), Wushu (GB27), and Weidao (GB28). The Tuina techniques and acupoint selection were based on a standardized national textbook (32). Each procedure was performed for approximately 3–6 min, and the three procedures constituted one complete session, lasting about 20 min. The manipulation intensity was standardized to achieve moderate pressure, defined as patient tolerance without pain. All procedures were conducted by trained practitioners. Treatments were administered three times per week for 8 weeks. The anatomical locations of the acupoints are shown in (Figure 3).

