#### Core stability training group

2.6.2

The CST protocol was developed based on established core stabilization principles and evidence-based recommendations for the management of chronic low back pain and LDH (6, 33). Specifically, the program was designed to progress from diaphragmatic breathing to quadruped contralateral limb extension and standing anti-rotation exercises. The exercise progression was informed by evidence supporting the role of breathing control, deep trunk muscle activation, and progressively challenging stabilization tasks in core stability training (34–36). The selected exercises were intended to facilitate coordinated activation of the transversus abdominis, multifidus, and related trunk musculature while maintaining safety and feasibility for patients with LDH. Firstly, all participants received standardized lumbar spine health education prior to the intervention. Subsequently, the exercises were performed under the supervision of a rehabilitation therapist. The exercises were carried out in the order of A–D (Figure 4), including diaphragmatic breathing training in the supine position, quadruped contralateral limb extension (bird-dog exercise), standing trunk rotation with elastic resistance, and balance training on an unstable surface. Each exercise was performed for three sets, with 10–15 repetitions or maintained for 6–10 s or approximately 1 min, depending on the specific task. A rest interval of 30–60 s was provided between sets and exercises to minimize fatigue. The total duration of each training session was approximately 20 min. Exercise intensity was adjusted according to participant tolerance to maintain a moderate level of exertion without exacerbating pain. Treatments were administered three times per week for 8 weeks.

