#### Combined Tuina and core stability training group

2.6.3

Firstly, all participants received the same standardized lumbar spine health education as described for the other two groups. Subsequently, the combined intervention consisted of sequential Tuina therapy followed by core stability training, as described above. The Tuina procedure was performed first, followed immediately by the core stability training within the same session. The total duration of each session was approximately 40 min. Treatments were administered three times per week for 8 weeks. The difference in intervention duration between groups will be treated as a potential confounding factor and will be included as a covariate in the linear mixed-effects models to control for its potential influence on the outcomes.

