### Statistical analysis

2.11

All statistical analyses will be performed using IBM SPSS Statistics (Version 27.0). Efficacy analyses will follow the intention-to-treat (ITT) principle, including all randomized participants. Continuous variables will be tested for normality and presented as mean ± standard deviation or median (interquartile range), as appropriate, while categorical variables will be expressed as counts and percentages. Baseline characteristics will be summarized descriptively without formal statistical comparisons. Primary and secondary outcomes will be analyzed using linear mixed-effects models, with group, time, and group-by-time interaction as fixed effects and subjects as random effects. Intervention duration (20 vs. 40 min) and baseline values of the outcome measures will be explicitly included as covariates to account for potential confounding effects. Therapist identity will be included as a random intercept to account for potential clustering effects. Model assumptions will be evaluated using residual diagnostics. If significant group-by-time interactions are detected, post-hoc pairwise comparisons with Bonferroni correction will be performed. Missing data will be handled using multiple imputation under the missing-at-random assumption. Safety analyses will include all participants who received at least one treatment, and adverse events will be compared using the chi-square test or Fisher's exact test, as appropriate. Sensitivity analyses, including complete-case analyses, per-protocol analyses, and analyses adjusted for intervention duration, will be conducted to assess the robustness of the primary outcome. All statistical tests will be two-sided, with a significance level set at *P* < 0.05, and 95% confidence intervals will be reported. Effect sizes (e.g., Cohen's d) will also be reported to facilitate interpretation of the clinical relevance of the findings.

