However, several limitations should be acknowledged. This is a single-center study with a relatively small sample size, which may limit generalizability. Blinding of participants and therapists was not feasible due to the nature of the interventions, which may introduce performance bias and expectation effects. Specifically, patient-reported outcomes (VAS, ODI, JOA, and SF-36) may be influenced by participants' perceptions and treatment expectations. To mitigate these biases, objective outcome measures—including musculoskeletal ultrasound, MRI, X-ray, and pressure biofeedback—will be assessed by independent evaluators blinded to group allocation, and statistical analyses will be conducted by investigators blinded to group allocation. Certain measurements, particularly ultrasound assessments, may still be subject to operator-dependent variability (44). Some mechanistic inferences rely on prior literature rather than direct measurement, and the absence of a sham or placebo control may further introduce expectation-related effects. The combined intervention group received twice the total intervention duration compared to monotherapy groups (20 vs. 40 min per session), although intervention duration will be included as a covariate, residual confounding cannot be entirely excluded. The upper age limit of 55 years restricts generalizability to older adults with LDH, and despite standardized training, some operator-dependent variability in Tuina procedures may remain. Future multicenter studies with larger sample sizes, longer follow-up periods, and time-matched control designs are warranted to confirm these findings and isolate the specific effects of the combined intervention. Overall, this study is expected to provide preliminary evidence and methodological guidance for integrating Tuina and core stability training in LDH management.

If proven effective, this combined approach may provide a practical and scalable rehabilitation strategy for patients with LDH in clinical settings.

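### Session duration is fixed by arm, so adjusting for it leaves the combined-versus-single contrasts undefined or unadjusted and removes none of the dose confounding

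*Protocol article*

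**What the plan says.** Three subsections of the protocol article fix session length by arm:

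- Section 2.6.1, Tuina: "the three procedures constituted one complete session, lasting about 20 min".
- Section 2.6.2, core stability training: "The total duration of each training session was approximately 20 min".
- Section 2.6.3, combined arm: "The total duration of each session was approximately 40 min".

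Section 2.6.3 then treats this as something a model can correct: "The difference in intervention duration between groups will be treated as a potential confounding factor and will be included as a covariate". Section 2.11 specifies linear mixed models with group, time and group-by-time as fixed effects and adds: "Intervention duration (20 vs. 40 min) and baseline values of the outcome measures will be explicitly included as covariates". Among the sensitivity analyses it lists "per-protocol analyses, and analyses adjusted for intervention duration, will be conducted to assess the robustness of the primary outcome". The limitations in the Discussion say that "although intervention duration will be included as a covariate, residual confounding cannot be entirely excluded".

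The covariate is written with two values, 20 and 40. Nowhere does the article say that individually recorded minutes would be used instead.

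**The concern.** A covariate can separate its own effect from that of treatment only if it varies within arms or overlaps between them. Here it does neither. All participants in the two single-therapy arms have 20 and all in the combined arm have 40, so duration is a recoding of whether the participant was randomised to the combination. It is also part of the assigned treatment, not a baseline characteristic that happens to differ between groups.

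The Introduction asks whether the combination is better than each therapy alone. Adjusting for duration affects exactly those two comparisons. Either the adjustment does nothing and the result is reported as adjusted, or it takes the combined-arm effect out of the model. In both cases a reader would believe that extra contact time had been largely dealt with when it had not been touched.

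**Working it through.** **Inputs.** Durations of 20, 20 and 40 min (sections 2.6.1 to 2.6.3); 32 participants per arm (section 2.5); fixed effects and covariates (section 2.11); ultrasound measured before and after the intervention only (section 2.7.1.1).

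**The plan's own figure.** The article gives no number for the duration adjustment. Its sample size does reproduce: a two-sample t-test with d = 0.78, two-sided α = 0.05 and power 0.80 needs 26.8, so 27 per group. Then 27/0.85 = 31.8, so 32 per group and 3 × 32 = 96. It is not affected by what follows.

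**Step 1: aliasing.** Let S and C be indicators for core training and the combination, with Tuina as reference, B the baseline value and D the duration. Then

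D = 20 + 20·C,

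and the correlation of D with C is 1.0.

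**Step 2: week-8 model with baseline as covariate.**

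E(Y) = a + b₁S + b₂C + gB + dD

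Substituting for D gives

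E(Y) = (a + 20d) + b₁S + (b₂ + 20d)C + gB.

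The data identify only a + 20d, b₁, b₂ + 20d and g. That is four quantities for five parameters: 5 columns, rank 4. Given duration:

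| Contrast | Parameter | Estimable? |
|---|---|---|
| Combined − Tuina | b₂ | No |
| Combined − core training | b₂ − b₁ | No |
| Core training − Tuina | b₁ | Yes |

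**Step 3: repeated-measures versions.** Counting non-redundant columns with the baseline covariate kept:

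| Outcome rows | Rank without D | Columns with D | Rank with D |
|---|---|---|---|
| Week 8 only | 4 | 5 | 4 |
| Two time points | 7 | 8 | 7 |
| Three time points | 10 | 11 | 10 |

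In every layout the combined-versus-Tuina and combined-versus-core contrasts at week 8 are not estimable once D is included. The group-by-time contrasts (differences in change) do stay estimable. D is constant over time, so dD appears in both terms of each difference and cancels: the contrast is the same number with or without D. If a duration-by-time term were added, these contrasts would be lost as well.

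**Step 4: numerical illustration.** One data set of 96 was simulated with an assumed combined-arm effect of 0.2 and residual SD of 0.2. Fitted values were identical with and without D. The combined-arm coefficient depended only on how the redundancy was resolved:

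- D omitted: 0.153.
- D kept and the arm indicator set to zero: arm effect 0, with 20 × the duration slope = 0.153.
- Minimum-norm solution with both kept: −0.259.

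Only the sum b₂ + 20d = 0.153 is identified. The split between arm and duration is arbitrary.

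**Step 5: the sensitivity analysis.** The main model already contains duration, so the duration-adjusted sensitivity analysis repeats the same unidentified adjustment and cannot test robustness.

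**The case against.** The strongest reply is that section 2.11 tests the group-by-time interaction first and makes pairwise comparisons conditional on it. With two or more outcome times, that interaction is estimable and unaffected by duration. This is correct, and it limits the claim of non-estimability to group contrasts at a time point or averaged over time. It does not help the plan, because an unaffected contrast is an unadjusted one. If baseline enters only as a covariate, the primary ultrasound outcome has a single post-baseline value, no interaction term exists, and the week-8 contrast is the only target.

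Second, software may simply drop duration, which leaves the valid randomised contrast with only the label wrong. That is possible, and the article does not show which term would go. A pre-specified primary analysis should not depend on it.

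Third, the Discussion discloses that the combined arm receives twice the session time, and it calls for time-matched designs in future. That deserves credit. It still presents the covariate as a working adjustment with only residual confounding left.

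Fourth, neither component is doubled in the combined arm, so the unadjusted comparison of packages is a legitimate answer to the stated aim. This stands. The damage is to the model as specified and to attribution of the effect, not to the randomised comparison itself.

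A side issue is blinding. Section 2.4.2 says "unblinding will occur only after completion of all statistical analyses", but a column reading 40 for one coded group identifies the combined arm. The other two arms stay masked and the layout of the analysis file is not described, so the conclusion does not rest on this.

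**Conclusion.** The concern holds: the adjustment is wrong as written. Duration is an exact function of arm. Its inclusion makes two of the three pairwise group contrasts at week 8 non-estimable, and it leaves any surviving group-by-time contrast numerically unchanged. It removes none of the confounding with contact time on any reading. The confounding is complete, not residual, and no analysis of this design can separate the content of the combination from its additional 20 min per session (40 − 20).

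This assumes that the covariate is the two-valued planned duration, as section 2.11 writes it. If recorded individual minutes were intended, the text would have to say so. That variable would be measured after randomisation, would be a consequence of treatment, and would still be nearly collinear with arm.

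**What to change.** Make four text changes in three sections:

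1. Section 2.6.3: delete the sentence that makes duration a covariate, and state instead that session time differs by design.
2. Section 2.11, main model: remove intervention duration and keep the baseline value of the outcome.
3. Section 2.11, sensitivity analyses: remove the duration-adjusted analysis.
4. Discussion: replace the residual-confounding clause with a statement that session time is completely confounded with the combined arm, so that a positive result cannot be attributed to the combination as opposed to the extra contact time. Keep the call for time-matched designs.

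In the objectives or section 2.11, define the comparison as the effect of the 40-min combined package versus each 20-min single therapy. With duration removed, the week-8 model has rank 4 for 4 parameters and all three pairwise contrasts are estimable.

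The cost is small: no new data, no change to the interventions, and the sample size stays at 27 per group before dropout and 32 after. Because this changes a pre-specified analysis of a registered trial, it should be recorded as a dated amendment before database lock. Recruitment is planned to run to 1 November 2027. The price is a more modest conclusion about what caused any benefit.

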### Interventions

2.6

All interventions in this study will be administered by professionally trained therapists. Tuina therapy will be performed by experienced Tuina practitioners, while core stability training will be guided by senior rehabilitation therapists. To ensure consistency of the interventions, both therapists will receive standardized training and pass a clinical trial operation assessment prior to the initiation of the study. All participants will receive individualized treatment three times per week (once every other day) for a total duration of 8 weeks. During the trial period, participants will be requested to refrain from receiving other treatments related to the study interventions, such as medications, acupuncture, or physical therapy. Participants who receive prohibited concomitant treatments will be withdrawn from the intervention but retained for intention-to-treat analysis. If additional treatments are deemed medically necessary, the trial will be terminated for that participant, and the relevant information will be documented in the case report form (CRF).

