#### Intervention delivery and fidelity

2.8.1

All interventions will be delivered by licensed practitioners with at least 3 years of clinical experience. Prior to trial initiation, all practitioners will undergo standardized training and pass a clinical trial operation assessment to ensure consistency in intervention delivery, including treatment intensity, frequency, and procedures according to the study protocol.

All Tuina treatments will be delivered by the same licensed Tuina practitioner, and all core stability training sessions will be supervised by the same licensed rehabilitation therapist throughout the study. Although therapist blinding is not feasible due to the nature of the interventions, therapists will strictly follow standardized treatment manuals and will not be involved in outcome assessment, data collection, or statistical analysis.

To ensure protocol adherence and minimize variability in treatment delivery, regular supervision sessions will be conducted throughout the study. Treatment fidelity will be monitored using a standardized checklist (Supplementary Table S2) and periodic supervision. In addition, a random sample of treatment sessions will be independently observed or recorded for fidelity evaluation. Adherence to the intervention protocol will also be documented throughout the study.

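### The therapist random intercept in 2.11 cannot adjust for clustering, because with one practitioner per discipline therapist is fully determined by arm

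*Protocol article*

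**What the plan says.** Section 2.11 sets out a linear mixed model for primary and secondary outcomes, "with group, time, and group-by-time interaction as fixed effects and subjects as random effects". It then adds: "Therapist identity will be included as a random intercept to account for potential clustering effects". Baseline values enter as a covariate. The route to arm comparisons is: "If significant group-by-time interactions are detected, post-hoc pairwise comparisons with Bonferroni correction will be performed".

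Section 2.8.1 fixes who delivers treatment. On the manual therapy it states: "All Tuina treatments will be delivered by the same licensed Tuina practitioner". The exercise programme is likewise in the hands of one person: "all core stability training sessions will be supervised by the same licensed rehabilitation therapist throughout the study". Section 2.6.3 describes the combined arm: "The Tuina procedure was performed first, followed immediately by the core stability training within the same session".

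Section 2.6 is looser: "Tuina therapy will be performed by experienced Tuina practitioners, while core stability training will be guided by senior rehabilitation therapists". Its following sentence, on training, then refers to the therapists as a pair.

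**The concern.** A random intercept for therapist separates therapist variation from treatment only if several therapists work within an arm, or if therapists cross arms in a way that the arm effects do not already describe. Here neither holds. A reader of 2.11 would believe that therapist effects had been modelled, when the design gives the model nothing to estimate them from. The limitations in the Discussion mention some remaining operator-dependent variability in Tuina, but not that practitioner and treatment are inseparable.

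The second matter at stake is precision. If the software returned a non-zero value for a variance on which the data are silent, that value would feed into the standard error of some arm comparisons.

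**Working it through.** **The plan's own figure.** A two-sample t-test by the noncentral t, with d = 0.78 and two-sided α = 0.05 (section 2.5), gives power 0.788 at 26 per group and 0.803 at 27. So 27 per group reproduces, and 27/0.85 = 31.8 rounds up to 32 per group, 96 in total. The calculations below use 27 per arm and residual SD 1.

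**Therapist by arm (2.8.1 and 2.6.3).** Call the Tuina practitioner A and the rehabilitation therapist B.

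- Tuina arm: A for every participant.
- Core stability arm: B for every participant.
- Combined arm: A and B for every participant.

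**Identifiability.** The fixed-effects design (intercept, two arm indicators, baseline) has rank 4. Adding the therapist columns leaves the rank at 4 under each of four codings of the combined arm: multiple membership (A + B), half weights, a separate third level, or assignment to A alone. The therapist columns lie in the span of the arm effects.

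**Likelihood.** On simulated data with multiple-membership coding, over therapist variance τ² = 0, 0.01, 0.05, 0.1, 0.5 and 1:

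- The REML log-likelihood is −41.188097 at every value, so it carries no information on τ².
- The ML log-likelihood falls from −34.2215 at τ² = 0 to −38.0909 at τ² = 1, so the ML estimate is zero.
- The estimated arm effects are the same at every value.

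**Standard error at a time point.** For combined minus a single-therapy arm, approximately

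SE = √(2/27 + c·τ²),

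where c = 1 for multiple membership, 0.5 for half weights and 2 for a third level. With the combined arm coded to A, c = 0 for combined minus Tuina and c = 2 for combined minus core. Power by normal approximation is Φ(0.78/SE − 1.96).

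The documents give no value for τ. With an **assumed** τ = 0.2 (τ² = 0.04):

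| Coding of combined arm | SE | Power at d = 0.78 |
|---|---|---|
| No therapist term | √0.0741 = 0.272 | 82% |
| Half weights | √(0.0741 + 0.02) = 0.307 | 72% |
| Multiple membership | √(0.0741 + 0.04) = 0.338 | 64% |
| Third level | √(0.0741 + 0.08) = 0.393 | 51% |

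Range over the assumption, multiple membership: τ² = 0.01, 0.05, 0.1, 0.5 and 1 give SE 0.290, 0.352, 0.417, 0.758 and 1.036, and power 77%, 60%, 46%, 18% and 11%.

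**Group-by-time contrast.** With baseline and week 8 both in the response, a participant's therapist intercept is the same at both times and cancels from the change. The SE of the combined-minus-Tuina interaction is 0.272 at τ² = 0, 0.05, 0.1 and 1. The SE of the week-8 difference in the same model goes from 0.272 to 0.352, 0.417 and 1.036.

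**The case against.** The strongest reply is that the term is merely redundant. Section 2.11 reaches pairwise comparisons only through the group-by-time interaction, and with baseline in the response that test is untouched. Under ML the variance goes to zero and the model becomes the one without the term. A REML estimate of zero would be equally harmless, and a convergence failure would be seen. All of this stands, and it limits the harm. It does not rescue the sentence in 2.11, because in each of these cases no adjustment for clustering takes place.

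The exposure does not vanish either. Section 2.11 also makes baseline a covariate, and 2.7.1.1 schedules ultrasound before and after the intervention. If baseline is only a covariate, the primary outcome has a single post-baseline value and the week-8 arm contrast is the comparison of interest. That contrast is the kind exposed under REML.

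A second reply is that the plurals in 2.6 imply several practitioners per discipline, which might make the variance partly estimable. But 2.6 itself goes on to speak of a pair, and 2.8.1 is explicit.

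A reader might go further and infer that the planned software will return an arbitrary value, or that therapist identity unblinds the analyst. The documents establish neither. They do not state the estimation method, and the software's behaviour with this model was not tested. Section 2.4 provides for coded allocation, and therapist labels could be coded too. The 20 versus 40 min covariate would identify the combined arm in any case.

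**Conclusion.** The point holds in limited form. On the text of 2.8.1 and 2.6.3, therapist is fixed by arm, its variance is not identifiable, and the adjustment stated in 2.11 cannot happen. This rests on 2.8.1 being the operative statement of who delivers treatment.

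The effect on precision is conditional. It needs REML, a non-zero variance returned by the software, and a between-arm contrast at a time point. Its size depends on an assumed τ and on the coding of the combined arm, and under one coding combined minus Tuina is not affected at all.

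It is tempting to conclude that the standard errors of all arm contrasts are arbitrary, or that the trial's power falls to 51%. The documents do not support that. The interaction contrast is unaffected with baseline in the response, and 51% requires both τ = 0.2 and the third-level coding. The coding that matches the design as described, with both practitioners in the combined arm, gives about 64% at the same τ, or about 72% if the two are half-weighted. This should be fixed, but it does not undermine the trial.

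**What to change.** - Delete the therapist random intercept from 2.11.
- Reconcile the plural wording in 2.6 with the single practitioner and single therapist in 2.8.1. If several per discipline were in fact intended, 2.8.1 must say so, and the term could then be reconsidered.
- Add to the limitations that practitioner and treatment effects are completely confounded, so the results are conditional on these two practitioners.

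The cost is one sentence deleted, one wording correction and one limitation added. Sample size, data collection and point estimates do not change. Recruitment is planned to run to 1 November 2027 (2.1), so this can be done by a dated amendment before database lock.

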Core stability training, as a representative form of exercise-based rehabilitation, directly targets the neuromuscular mechanisms underlying spinal stability. It aims to improve coordination and activation of deep stabilizing muscles, thereby enhancing spinal and pelvic stability. By strengthening these muscles, core stability training can reduce excessive loading on superficial lumbar structures and address instability caused by muscle imbalance or fatigue (17, 18). Previous studies have demonstrated that core stability training can significantly reduce pain and improve functional performance in patients with LDH (19, 20). Nevertheless, exercise-based interventions alone may have limited effects on soft tissue relaxation and pain modulation, particularly in the early stages of treatment. Given their distinct yet complementary mechanisms, Tuina therapy and core stability training may exert synergistic effects in the management of LDH. Tuina primarily improves soft tissue condition and alleviates pain, whereas core stability training enhances neuromuscular control and spinal stability. However, current evidence remains insufficient to determine whether the combined intervention is more effective than either therapy alone, particularly in improving lumbar stability and related clinical outcomes.

Consequently, the present study proposes to conduct a randomized controlled clinical trial with blinded outcome assessment and data analysis to further validate the effectiveness of the combined intervention. A combination of musculoskeletal ultrasound, imaging assessments, pressure biofeedback unit assessment, and patient-reported outcome measures will be used to comprehensively evaluate lumbar stability and clinical outcomes. This approach will help determine whether the combined therapy provides superior benefits compared with single interventions.

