### Sample size calculation

2.5

The sample size was calculated using G*Power 3.1. The calculation was based on the primary outcome, namely the muscle activation ratio of the transversus abdominis assessed by musculoskeletal ultrasound. Previous studies in patients with low back pain have reported medium-to-large effect sizes (Cohen's d ≈ 0.71) for changes in transversus abdominis activation following core stability training (30). Furthermore, ultrasound studies in patients with LDH have demonstrated significant alterations in core muscle morphology (31), suggesting that similar or larger effects may be anticipated in this population. Therefore, a conservative effect size of 0.78 was assumed for the present study.The selected effect size was based on previous studies reporting moderate-to-large effects in similar populations and was conservatively estimated.

With a two-sided α of 0.05 and a power (1−β) of 0.80, the required sample size was 27 participants per group. Considering a 15% dropout rate, the final sample size was set at 96 participants, with 32 participants in each group.

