### Outcomes

2.7

The efficacy evaluation in this study will focus on the primary and secondary outcome measures assessed at baseline and immediately after the intervention. In addition, selected clinical outcomes, including pain intensity and functional status, will be reassessed at the 1-month follow-up using the VAS and ODI to evaluate the persistence of treatment effects. Follow-up assessments will be conducted by independent outcome assessors who are blinded to group allocation.All outcome assessments will be conducted by independent researchers who are blinded to group allocation and are not involved in other aspects of the study. The schedule of enrolment, interventions, and assessments is presented in (Figure 5).

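### For VAS and ODI, pairwise tests wait on a group-by-time interaction in a baseline-adjusted model whose time levels are not listed; on one reading a maintained benefit almost never opens that gate, on the other it usually does

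*Protocol article*

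**What the plan says.** The Introduction puts the trial's question as a comparison of arms: "This approach will help determine whether the combined therapy provides superior benefits compared with single interventions". Section 2.7 (Outcomes) limits most measures to two occasions, describing "primary and secondary outcome measures assessed at baseline and immediately after the intervention". It adds a third occasion for pain and disability only, which "will be reassessed at the 1-month follow-up using the VAS and ODI to evaluate the persistence of treatment effects".

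Section 2.11 (Statistical analysis) prescribes one linear mixed model for all primary and secondary outcomes, "with group, time, and group-by-time interaction as fixed effects and subjects as random effects". In the same model, "baseline values of the outcome measures will be explicitly included as covariates", together with intervention duration (20 or 40 minutes). The only route to pairwise tests that the section states is: "If significant group-by-time interactions are detected, post-hoc pairwise comparisons with Bonferroni correction will be performed". The group term opens no comparison. The levels of time are not given.

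**The concern.** Whether combined therapy beats each single therapy on VAS and ODI, and whether that advantage lasts, is a question about the size of the between-arm difference at week 8 and at 1 month. A group-by-time interaction answers it only if baseline is one of the time levels. Once baseline moves to the covariate side, as section 2.11 says, two response visits remain. The null hypothesis of the interaction is then that the between-arm difference is the same at both. A large, fully kept benefit satisfies that null exactly. A benefit that disappears violates it.

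On that reading the rule favours the pattern that the 1-month visit was added to rule out. On the other possible reading it does not. The two readings give opposite results, and the choice between them should not be left until data are in hand.

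**Working it through.** **Inputs from the protocol.** Three arms, 1:1:1; two-sided 0.05; power 0.80; effect size 0.78; 27 per group before and 32 per group after 15% dropout (section 2.5).

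**Assumptions.** The 0.78 SD is the protocol's figure for the ultrasound outcome and is borrowed here for VAS and ODI. The outcome SD is 1. The correlation ρ between any two visits is 0.6, with 0.4 and 0.8 as the range. Only the combined arm is better. Bonferroni is taken over the three arm pairs (0.05/3). The therapist intercept is left out.

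**The plan's own figure.** "With a two-sided α of 0.05", a two-sample t-test at 0.78 SD has power 0.788 with 26 per group and 0.803 with 27. So 27 reproduces, and 27/0.85 = 31.8 gives 32 per group, 96 in total.

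**Reading A: response visits are week 8 and 1 month, baseline is a covariate.** With two balanced visits and a random intercept, the interaction test is a one-way F-test of arm on the change D from week 8 to 1 month.
- Var(D) = 2(1 − ρ) = 0.8 at ρ = 0.6.
- If a fraction f of the benefit is lost, the arm means of D are 0, 0 and 0.78f. Their squared deviations sum to (2/3)(0.78f)².
- Noncentrality: λ = 27 × (2/3)(0.78f)² / 0.8, on 2 and 78 degrees of freedom.

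| Benefit at 1 month | λ at ρ = 0.6 | Gate opens, ρ = 0.6 | ρ = 0.4 to 0.8 |
|---|---|---|---|
| Fully kept (f = 0) | 0 | 5% | 5% to 5% |
| Half lost (f = 0.5) | 3.42 | 35% (36% simulated) | 24% to 63% |
| All lost (f = 1) | 13.69 | 91% | 76% to 99.8% |

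The first row depends on neither the effect size nor ρ, because λ is zero whatever the benefit. A simulated maintained benefit of 1.5 SD opened the gate in 5.4% of trials.

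**Consequence for the week-8 contrast under full maintenance.** The baseline-adjusted contrast of combined versus one single therapy has standard error √(2(1 − 0.36)/27) = 0.218. Its noncentrality is 0.78/0.218 = 3.58, against a critical value of 2.45 at 0.05/3 (77 df). Power is about 87% (86% simulated). Requiring the gate first cuts this to 3.9% in simulation.

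**Reading B: baseline is also a response row.** The interaction now has 4 and 156 degrees of freedom. With the benefit present at both later visits, λ = 27 × 0.78² × (2/3)(2/3) / (1 − ρ). At ρ = 0.6, λ = 18.25 and the gate opens in about 94%. At ρ = 0.4, λ = 12.17 and it opens in about 80% (78% simulated).

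**Duration.** Coding the two-visit model with intercept, two arm terms, time, two interaction terms, baseline and duration gives 8 columns of rank 7. Duration is 40 minutes in the combined arm and 20 in both others, so arm determines it exactly. A duration-adjusted difference between the combined arm and either single-therapy arm cannot be estimated. The interaction itself is unaffected, so the gate results above stand.

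**The case against.** The strongest objection is that reading B may be the intended one. Section 2.11 applies a single model with a group-by-time term to every outcome. Most outcomes, the primary included, have only one value after baseline, so for them the interaction exists only if baseline is a time level. Section 2.1 lists baseline among the assessment times, and section 2.7.2.3 speaks of within-group comparisons before and after treatment. Nor does placing baseline on both sides of the model close the gate: a fit of that literal version opened it in 95% of 200 runs under full maintenance (7% under no effect, with some fits at the variance boundary). This stands. A reader might infer that the plan certainly blocks the VAS and ODI comparisons whenever a benefit lasts. The documents do not support that, because the time levels are open.

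A reader might also infer that a closed gate means no between-arm result at all. That goes too far. Section 2.7.2.3 promises between-group comparisons without condition, and section 2.11 promises confidence intervals and effect sizes. Only the formal post-hoc tests are gated.

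Finally, time levels are detail that an article may leave to an analysis plan. That does not dispose of the point, because the covariate and the gate are both stated, and on the reading that the covariate implies, their combination gives a wrong result.

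**Conclusion.** The point holds conditionally. If the response visits for VAS and ODI are week 8 and 1 month, the gate tests change after treatment, not benefit. It then opens at its 5% error rate for a maintained effect of any size, and that figure needs no assumption about effect or correlation. The 36% and 91% for partial and complete loss rest on 0.78 SD, ρ = 0.6 and 27 per arm. So does the fall from about 86% to 3.9% in the chance of a significant week-8 contrast. If baseline is also a response row, most of the loss disappears (gate about 94%, or 78% at ρ = 0.4), at the price of using baseline twice. These are secondary outcomes, but they alone carry the persistence question, so the text should be settled before the analysis.

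**What to change.** In section 2.11 and the analysis plan, for VAS and ODI:

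1. State that the response visits are week 8 and 1 month, with the baseline value as a covariate.
2. Remove the interaction as a condition for pairwise tests.
3. Remove intervention duration from the model. Without this step the contrasts with the combined arm are not estimable as adjusted effects. The difference in session length remains a limit on interpretation, which the Discussion already acknowledges.
4. Test combined versus Tuina and combined versus core stability training at week 8 and at 1 month, with the planned Bonferroni correction.
5. Report the interaction only as a description of whether the difference changes after treatment ends.

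The cost is a few sentences before database lock, with the same data and software. The omnibus layer is lost, but Bonferroni alone controls the error rate of the pairwise family at each visit. It does not extend across visits or outcomes.
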